### 2.4. Interventions

The V-CARE group intervention programme is described based on the Template for Intervention Description and Replication (TIDieR) checklist (Figure S1).

#### 2.4.1. V-CARE (Virtual CAre After REsuscitation)

The intervention focuses on providing early cardiac-arrest-related education, promoting the development of coping skills, encouraging peer support, and signposting survivors and key supporters to relevant resources/services.

The V-CARE programme involves 4 structured sessions, one a week, each lasting around one hour, supported by PowerPoint presentations (File S1). The content focuses on providing education on cardiac arrest and secondary prevention, addressing practical problems (for instance, returning to driving, travelling, living with an implantable cardioverter defibrillator (ICD), etc.) and understanding/coping with fatigue, cognitive changes, and psychological difficulties. As multiple sites in each country are expected to take part in this study, groups will be formed as soon as 3 to 6 patients have been recruited, although smaller groups could be formed if required. Group size will usually be between 4 and 12 participants. The aim is for the intervention to be delivered early to each group, starting around 2 and 3 months after hospital discharge; however, it is expected that it may be delivered to some groups up to—but not beyond—6 months post-discharge.

Each session includes broadly equal time for presentation, questions, and discussion, with the aim of encouraging participants to develop self-management skills. A printout of the PowerPoint slides used in each session is provided in Supplementary Material.

A single, designated healthcare professional will serve as a facilitator for each group and will be present for all sessions, having been trained by the study team; it is anticipated that it will be delivered by either a clinical psychologist or an occupational therapist, but a clinical nurse specialist could also manage a group. A cardiologist or cardiology resident will attend the first session to answer generic, cardiac-arrest-related questions.

#### 2.4.2. Digital Information Booklet

This intervention, also co-developed with a patient group, consists of an information booklet focused on providing information and coping strategies for fatigue, memory, low mood, anxiety, and cognitive problems after a cardiac arrest. Whereas the content is similar to that covered in the V-CARE arm, these patients are not included in a group and as such do not have access to peer support or to guided discussions and reflections as provided in the group setting. In this intervention arm, tolerability will be assessed by the proportion of participants who complete the post-intervention outcome measures; additionally, participants will be asked to self-report whether they read or used the booklet. A copy of this intervention is provided in the Supplementary Material (File S2).

### 2.5. Outcomes and Outcome Measures

#### 2.5.1. Primary Outcomes

The primary outcomes are the feasibility and tolerability of taking part in a psychoeducational virtual group for OHCA survivors and key supporters.

Feasibility of recruitment will be defined as the number of patients who consented out of all the eligible patients (consent rate).

Tolerability will be measured by the completion rate for those recruited and adherence to the intervention protocol (that is, the number of sessions attended out of the total sessions).

#### 2.5.2. Secondary Outcomes

Satisfaction with care will be assessed by the Client Satisfaction Questionnaire-8 (CSQ-8)—for both patients and key supporters. For self-management the Self-management Assessment Scale (SMASc) will be used—patients only [42]. In the control group, patients will be asked to complete outcome measures around a month after being sent the digital booklet—replicating the month-long length of the V-CARE intervention.

#### 2.5.3. Additional Outcomes

Where available, results of the detailed follow-up sub-study of STEPCARE at 6 months and 12 months will also be used in the analysis of V-CARE; they include measures of cognition (MoCA, SDMT, MFIS IQCODE-CA—patients only), burden (ZBI—key supporters), anxiety and depressive symptoms (HADS—both), post-traumatic stress symptoms (PCL-5—both), health-related quality of life (EQ-5D-5L, WHODAS 2.0—both), life satisfaction (both), and detailed questions about return to work/rehabilitation (patient only) [43].

### 2.6. Data Collection, Statistical Analyses, and Sample Size

For primary outcomes, descriptive statistics will be used to report on recruitment and retention rates. Continuous variables will be presented as the mean (SD) or median (IQR) depending on the distribution of data and percentages for categorical variables.

Using the methodology described by Lewis et al. [44], we set up hypothesis testing around progression criteria that tests against being in the ‘red zone’ based on an alternative of being in the ‘green zone’. Specifically, we aim to investigate that a true feasibility/tolerability outcome is not greater than the upper ‘red limit’ (null hypothesis) vs. a true feasibility/tolerability outcome that is greater than that (alternative hypothesis). Criteria for success and a traffic light system to identify the need for amendment for a fully powered trial are as follows:Feasibility: At least 35% of patients screened as eligible should be recruited into the trial (green), but the trial will not be feasible if recruitment uptake is 20% or less (red). Recruitment of between 20% and 35% may require amendments (amber).Tolerability: The drop-out rate of patients recruited in the trial should be 20% or less (successful completion of the trial is defined as taking part in at least 3 out of 4 sessions of the intervention and complete outcome measures). A drop-out rate of 40% or more will indicate that the full trial is not feasible (red), with a percentage between 20% and 40% suggesting that amendments may be required (amber).Satisfaction with care: No more than 30% of participants in the V-CARE arm should score less than 24/32 on the CSQ-8 (green); if more than 60% of participants score less than 24/32, this will indicate that the trial is not feasible (red), with a percentage between 30% and 60% suggesting that amendments to the protocol may be required (amber) (Figure 1).

A sample size calculation using a one-tailed test with alpha = 0.05 and beta = 0.9 identifies that with reference to the three criteria highlighted in this section, respectively, 78, 131, and 143 participants would be needed to be screened in order to meet the individual power requirement of > 90% (with regard to the second and third criterion, this is based on the assumption of only 35% of screened patients being actually randomized (2), and only half of these patients being in the intervention arm (3)). For this reason, we aim to screen at least 145 participants and recruit at least 50 (25 in each arm). This sample size is considered adequate to estimate key parameters to inform the design of an RCT.

To assess differences between two groups, the analyses will be conducted using independent data, with tests appropriate to the distribution of the data (independent *t*-test or Mann–Whitney U test). Estimated effect sizes (with 95% confidence intervals) for difference will be calculated. All *p*-values will be unadjusted for multiple comparisons due to the exploratory design [45]. Multi-variable logistic regression models will be used to evaluate the associations between disease severity, sociodemographic variables, and outcome measures. Outcomes will be statistically controlled for potentially confounding variables such as age, sex, education, and length of intensive care stay. As this is a feasibility study, the study will be underpowered; therefore, no conclusions on the effectiveness of the intervention will be made. SPSS v 29.0 or above will be used to analyze the data.

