## Figures and Tables

**Figure 1 jcm-14-04429-f001:**
[figure not shown]
V-CARE pilot feasibility criteria using red–amber–green (RAG) thresholds. The figure presents absolute percentage thresholds across three pilot outcomes: feasibility (percentage of eligible patients recruited), tolerability (percentage of recruited patients dropping out), and satisfaction with care (percentage scoring below 24 out of 32 on the CSQ-8 questionnaire). Thresholds indicate decision-making guidance for progression to a full trial: green = criteria fully met (pilot feasible); amber = criteria partially met (pilot feasible with protocol amendments); and red = criteria not met (pilot not feasible without substantial changes).

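### The pilot is sized on a one-sided 5% test against the red limit, but the printed bands end red exactly at that null value and the protocol does not say which rule governs progression

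*Protocol article*

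**What the plan says.** Section 2.6 of the protocol article contains two devices for the progression decision.

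- **A test.** The null is that "a true feasibility/tolerability outcome is not greater than the upper" red limit, and the alternative is that it exceeds that limit. The sample size rests on this test: "A sample size calculation using a one-tailed test with alpha = 0.05 and beta = 0.9". The numbers 78, 131 and 143 are those that "would be needed to be screened in order to meet the individual power requirement of > 90"%. The plan is then to screen at least 145 and recruit at least 50, with 25 per arm.
- **Bands.** For feasibility, "At least 35% of patients screened as eligible should be recruited into the trial (green"), "the trial will not be feasible if recruitment uptake is 20% or less (red"), and "Recruitment of between 20% and 35% may require amendments (amber"). For tolerability, drop-out of 20% or less is acceptable and 40% or more is red. For satisfaction, at most 30% of the V-CARE arm scoring under 24 on the CSQ-8 is green, and more than 60% is red.

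Of Figure 1 the caption says: "The figure presents absolute percentage thresholds across three pilot outcomes". It presents the bands as guidance for progression and describes amber as feasible once the protocol is amended. No critical value is given, and nothing says how the test and the bands combine.

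**The concern.** The red/amber edge is the null value itself. An observed percentage just above a null value is almost no evidence against it, so a band that starts there cannot have the 5% error rate of a test of that null. Between the red limit and the critical value, the two rules give different answers: the test says red is not excluded, while the band says the trial is feasible with amendments.

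Feasibility and tolerability are the primary outcomes, and the plan disclaims conclusions on effectiveness, so progression is the main decision the pilot informs. With 34 of 145 recruited, for instance, the team would have to choose between the rules after seeing the data. A reader would also credit the decision with an alpha and a power that belong only to the test.

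A lesser point concerns scale. The null sentence uses one direction (not greater than the red limit), which suits recruitment and completion. The cut-offs for tolerability and satisfaction are printed as drop-out and low scores, where higher is worse.

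**Working it through.** **Inputs (section 2.6).** One-sided alpha 0.05. The stated beta of 0.9 is read as power 0.90, in line with the power requirement in the same sentence. On the success scale, red limit p0 and green limit p1 are:

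- recruitment 0.20 and 0.35;
- completion 0.60 and 0.80 (one minus drop-out of 40% and 20%);
- CSQ-8 of 24 or more, 0.40 and 0.70 (one minus 60% and 30%).

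Planned denominators are 145, 50 and 25. The 50 for tolerability follows the plan's own conversion, which uses the 35% randomized for criterion 2 and halves only for criterion 3. The 145 are taken as eligible patients.

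**Step 1: reproduce the plan's figures.** Smallest n for which an exact binomial test, rejecting when X ≥ r with P(X ≥ r | p0) ≤ 0.05, has P(X ≥ r | p1) ≥ 0.90:

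| Criterion | n | r | alpha | power | Screened | Stated |
|---|---|---|---|---|---|---|
| Feasibility | 77 | 22 | 0.045 | 0.905 | 77 | 78 |
| Tolerability | 45 | 33 | 0.045 | 0.901 | 45/0.35 = 128.6, so 129 | 131 |
| Satisfaction | 25 | 15 | 0.034 | 0.902 | 25/(0.35 × 0.5) = 142.9, so 143 | 143 |

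All three agree within 2 patients, which confirms that the red limits are the null values.

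**Step 2: critical values at the planned sizes.**

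| Criterion | Reject if | Observed % | alpha | power at p1 | One fewer: P at p0 |
|---|---|---|---|---|---|
| Feasibility | ≥ 38/145 | 26.2 | 0.042 | 0.991 | 0.063 (37) |
| Tolerability | ≥ 37/50 | 74 | 0.028 | 0.889 | 0.054 (36) |
| Satisfaction | ≥ 15/25 | 60 | 0.034 | 0.902 | 0.078 (14) |

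**Step 3: where the rules disagree.** The lowest not-red count by band follows from the edges. Exactly 20% recruited (29/145) is red, so 30. Exactly 40% drop-out (30/50 completers) is red, so 31. Exactly 60% low scorers (10/25 satisfied) is amber, so 10. Amber by band with red not rejected is therefore:

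- 30–37 of 145 recruited (20.7–25.5%);
- 31–36 of 50 completers (62–72%);
- 10–14 of 25 scoring at least 24 (40–56%).

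**Step 4: error of the bands with the truth exactly at the red limit.**

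- Feasibility: P(X ≥ 30 | 145, 0.20) = 0.451
- Tolerability: P(X ≥ 31 | 50, 0.60) = 0.446
- Satisfaction: P(X ≥ 10 | 25, 0.40) = 0.575. If exactly 60% counted as red, P(X ≥ 11) = 0.414.

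False green at the same point: P(X ≥ 51 | 145, 0.20) = 0.000015; P(X ≥ 40 | 50, 0.60) = 0.0022; P(X ≥ 18 | 25, 0.40) = 0.0012.

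**Step 5: deeper in the red zone, P(not red by band).**

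- Feasibility: 0.228 at a true 18%, 0.040 at 15%, 0.0001 at 10%.
- Tolerability: 0.197 at a true completion of 55%, 0.059 at 50%.
- Satisfaction: 0.370 at a true 35% scoring at least 24, 0.189 at 30%.

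**The case against.** The strongest reply is that no contradiction is shown. Section 2.6 puts the test and the bands side by side without saying that the bands implement the test. In a test of red against green, the null has to sit at the red limit. Figure 1 offers guidance only, and how the two combine may be set out in the cited methodology or in a fuller document. This stands in part: the text does not support saying that the bands are meant to carry out the test. But the article itself prints both rules, they disagree over a stated range of results, and only one of them has the stated alpha.

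Three stronger readings are tempting and not supported:

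- **Any truly red trial escapes red about half the time.** That rate holds only exactly at the red limit. It is the conventional point for a type I error, but the error falls quickly below it, as step 5 shows.
- **Red trials are declared green.** False green is about 0.2% or less, so the green edge is stricter than the test. The misclassification is red to amber, and amber still calls for amendments.
- **The null points the wrong way.** Section 2.5.1 defines tolerability through completion, for which the printed direction is right, and the null sentence does not name satisfaction. What remains is a mismatch of scale between the null and the printed cut-offs.

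One could also count tolerability on the 25 V-CARE patients, because it refers to sessions attended. The band error would then be 42.5%, the cut-off 20/25 and the power 0.62. The plan's sample-size conversion does not use that denominator.

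**Conclusion.** The concern holds as a missing rule between a test and a set of bands. With the truth at the red limit, the bands taken alone return not red with probability 45%, 45% and 58%, against actual levels of 4.2%, 2.8% and 3.4% for the exact test at the same sizes. The stated alpha and power describe the test and do not carry over to a decision read off the bands.

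This rests on the bands being applied to observed percentages, exact binomial tests, and achieved numbers equal to the planned 145, 50 and 25. The 58% also depends on exactly 60% low scorers counting as amber, as printed.

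**What to change.** State one rule in section 2.6 and Figure 1, with integer cut-offs. Red: the null is not rejected. Amber: it is rejected but the estimate falls short of the existing green limit. Green: it is rejected and the green limit is reached.

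| Criterion | Null, success scale | Leave red | Amber | Green (unchanged) |
|---|---|---|---|---|
| Feasibility | recruitment ≤ 20% | ≥ 38/145 | 38–50 | ≥ 51 |
| Tolerability | completion ≤ 60% | ≥ 37/50 | 37–39 | ≥ 40 |
| Satisfaction | CSQ-8 ≥ 24 in ≤ 40% | ≥ 15/25 | 15–17 | ≥ 18 |

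Say that the cut-offs will be recomputed at the achieved n. A softer alternative is to split amber at the critical value and label the lower part as red not excluded. If the bands alone are to decide, state that the 5% alpha and 90% power do not describe that decision.

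The cost is one paragraph and one figure. The amber zone narrows, so some borderline results become red. Power at the green limit stays at 0.99, 0.89 and 0.90. The tolerability figure is just under 90% because of discreteness: at n=51 the same cut-off of 37 gives alpha 0.044 and power 0.93.

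### The tolerability criterion pairs a completion rule that only V-CARE patients can meet with a denominator and a sample size that count both arms

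*Protocol article*

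**What the plan says.** All places are in the protocol article.

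- **Limits (Section 2.6).** Green: "The drop-out rate of patients recruited in the trial should be 20% or less". Red: "A drop-out rate of 40% or more will indicate that the full trial is not feasible (red". The test "tests against being in the ‘red zone’ based on an alternative of being in the ‘green zone".
- **Completion rule (Section 2.6).** A patient completes by "taking part in at least 3 out of 4 sessions of the intervention and complete outcome measures".
- **Denominator.** Section 2.5.1 and the Figure 1 caption, like the green limit above, refer to recruited patients without restriction to an arm. Section 2.5.1 also makes session attendance part of the tolerability outcome.
- **Booklet arm (Section 2.4.2).** These patients are not in a group. "In this intervention arm, tolerability will be assessed by the proportion of participants who complete the post-intervention outcome measures".
- **Sample size (Section 2.6).** A "one-tailed test with alpha = 0.05 and beta = 0.9" leads to 78, 131 and 143 screened for feasibility, tolerability and satisfaction, each with an "individual power requirement of > 90" per cent. The conversion from recruited to screened assumes "only 35% of screened patients being actually randomized (2), and only half of these patients being in the intervention arm (3"). The plan is to screen at least 145 and recruit at least 50, 25 per arm.

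**The concern.** Attending three of four sessions is possible only in the V-CARE arm, yet the denominator and the 131 cover everyone randomised. The satisfaction criterion, whose text names the V-CARE arm, is halved for allocation; the tolerability criterion, whose rule names the sessions, is not. Nothing in the article says whether the 20% and 40% limits apply to V-CARE or to the whole trial, or how the two arms' completion measures combine.

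Tolerability is a primary outcome, and a red result means that the full trial is judged not feasible. If the denominator stays open until the data are in, the same data could give different progression verdicts.

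**Working it through.** **Inputs (Section 2.6).** Red limit: 40% drop-out, so completion p0 = 0.60. Green limit: 20% drop-out, so p1 = 0.80. One-sided alpha 0.05. The stated beta of 0.9 is read as power 0.9. Uptake is 0.35, allocation 1:1 (Section 2.3), 25 patients per arm.

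**1. Reproduce the plan's figure.**
- Stated: 131 × 0.35 = 45.9, about 46 patients in both arms. In V-CARE alone it would be 131 × 0.175 = 22.9.
- Exact binomial: the smallest n with at least 90% power is 45 (reject at ≥33 completers; alpha 0.0446, power 0.9005). 45 / 0.35 = 128.6, so 129 screened, within 2 patients of 131.
- Normal approximation: n = [(1.645√(0.6 × 0.4) + 1.282√(0.8 × 0.2)) / 0.2]² = 43.5, so 44 recruited and 126 screened. With continuity correction: 48.3, so 49 recruited and 140 screened.
- Cross-check on satisfaction: 25 / (0.35 × 0.5) = 142.9, so 143, as stated.

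The 131 is therefore reproduced only with both arms counted.

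**2. Literal reading: the session rule applied to all recruited.** All 25 booklet patients fail, so drop-out is at least 25/50 = 50%. That exceeds 40% whatever happens in V-CARE, so the result is always red.

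**3. Pooled reading: sessions plus measures in V-CARE, measures alone in the booklet arm.** Exact power at 80% completion is 90.05% at n = 45, 88.6% at 46 and 88.9% at 50. The normal approximation gives 91.6% at 46 and 93.6% at 50.

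Now set true V-CARE drop-out at the red limit of 40%. The article gives no booklet drop-out rate, so it is assumed over a range. With X ~ Bin(25, 0.60) completers in V-CARE and Y ~ Bin(25, 1 − d) in the booklet arm, the test rejects red if X + Y ≥ 37. The observed rate is green if X + Y ≥ 40 and red if X + Y ≤ 30.

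| Booklet drop-out d (assumed) | Pooled true drop-out | Test rejects red | Observed green | Observed amber | Observed red |
|---|---|---|---|---|---|
| 0% | 20% | 92% | 59% | 41% | <0.1% |
| 5% | 22.5% | 80% | 40% | 60% | 0.1% |
| 10% | 25% | 64% | 25% | 74% | 0.9% |
| 15% | 27.5% | 48% | 14% | 83% | 3% |
| 20% | 30% | 32% | 7% | 85% | 8% |

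With V-CARE drop-out at 50% and booklet drop-out at 5%, the observed pooled rate is red only 1.8% of the time.

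**4. V-CARE-only reading, n = 25.**
- Exact rule: reject at ≥20/25, since P(X ≥ 20 | 0.60) = 0.029.
- Power: P(X ≥ 20 | 0.80) = 0.617. The normal approximation is Φ[(0.2√25 − 1.645√0.24) / 0.4] = 0.686; with continuity correction it is 0.593.
- Power reaches 90% only at a true completion of about 87%.
- Keeping 90% at 80% completion needs 45–46 V-CARE patients, that is 90–92 randomised and 45 / 0.175 to 46 / 0.175 = about 258–263 screened, against 50 and 145 planned.

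**The case against.** The best defence is that the plan is consistent on a pooled denominator. Section 2.5.1, the limits in Section 2.6 and the Figure 1 caption all speak of recruited patients, and Section 2.4.2 gives the booklet arm its own measure. The natural reading is then arm-specific completion, pooled. On that reading 131 is right to within 2 patients, and the halving was applied only where the text names the V-CARE arm. This stands.

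A reader might infer that the stated power of over 90% is simply wrong and is really 62%. The documents do not support that: 62% arises only if the criterion is restricted to V-CARE, which no section does. A reader might also infer that the trial suffers both low power and masking. It cannot: the first needs a V-CARE-only test and the second a pooled one.

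Two further points hold in part. Masking usually turns a red V-CARE result into amber rather than green; green is the likelier outcome only when booklet drop-out is near zero. And session attendance is reported under Section 2.5.1, so poor attendance would remain visible even though the traffic light would not show it.

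The defence does not remove the inconsistency. The completion rule as written cannot apply to half of its own denominator, and no section says how the two measures combine. The remark in Section 2.6 that the study is underpowered concerns effectiveness, not this criterion.

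**Conclusion.** The point holds as an internal inconsistency between the criterion and its sample size, not as an arithmetic error. Each available reading has a fault:

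- literally, the result is always red;
- pooled, the power is about as stated, but a V-CARE programme at its red limit would show as red at most 8% of the time;
- in V-CARE alone, the 131 and the power claim do not apply, and power is about 62% (59–69% by method).

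The pooled figures assume 25 per arm, independent patients and booklet drop-out of 0–20%. The V-CARE-only figures assume 25 patients and true completion of 80%. Because a primary outcome and a progression decision depend on it, the definition should be settled before outcome data are seen.

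**What to change.** Reconcile Sections 2.4.2, 2.5.1 and 2.6 and the Figure 1 caption as follows:

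- Apply the 20% and 40% limits to patients randomised to V-CARE, with the existing session-plus-measures rule.
- Report questionnaire return in the booklet arm separately, as Section 2.4.2 already describes.
- For this criterion, replace the 131 and its power claim with: 25 V-CARE patients, 60% completion rejected at ≥20/25, about 62% power at 80% completion.
- Give an exact confidence interval for V-CARE completion.

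If a pooled criterion is preferred, state the completion rule for each arm. Also require and report V-CARE completion against the same limits, so that a pooled result alone cannot give green.

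The cost is rewording and a less favourable stated power. No extra patients are needed unless the sponsor wants 90% power in V-CARE alone, which would mean about 258–263 screened.

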### 1.2. Study Aims

The primary aims are to investigate whether the Virtual Care After REsuscitation (V-CARE) intervention—a bespoke psychoeducational, remotely delivered intervention co-designed with cardiac arrest survivors and their key supporters—is feasible and tolerable 2 to 3 months post-discharge from hospital. A secondary aim is to explore whether participating in the V-CARE intervention leads to beneficial effects in self-management skills and higher satisfaction with the treatment received, compared to a control group receiving a digital information booklet only.

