### 2.3. Study Population and Randomization

In addition to the criteria needed for taking part in STEPCARE, OHCA survivors eligible to take part in V-CARE are also required to have an mRS ≤ 3 at the 30-day follow-up and (a) must not have a diagnosis of dementia that would impact their ability to participate and benefit from the sessions and complete baseline/outcome measure (based on a clinician’s evaluation and/or self-report by the patient or family) and (b) must not be actively psychotic/experiencing any other serious acute mental health condition that would affect their participation in this study, based on clinical evaluation.

When recruited, consenting patients will be encouraged to take part in the study together with a ‘key supporter’; however, this will not be a requirement.

Consenting patients will be randomized on an equal basis (1:1) to the V-CARE arm or to the information booklet arm. V-CARE has a randomized block design with a separate randomization list in each country, completed by a local lead site. Custom-built software was developed using Python (v3.12.7) and the Tkinter library to allocate patients into two study conditions—V-CARE or the digital information booklet. A computer-generated pseudo-randomized list with 25 sets of 2 unique numbers per set was pre-generated using an online randomization tool [https://www.randomizer.org/] (accessed on 7 October 2024) to ensure an unbiased allocation process.

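### The exploratory SMASc comparison uses the post-intervention score alone; adjusting for a pre-intervention SMASc score would make it more precise at little or no cost

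*Protocol article*

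**What the plan says.** Section 1.2 gives the aim: "A secondary aim is to explore whether participating in the V-CARE intervention leads to beneficial effects in self-management skills", together with higher satisfaction, compared with the booklet arm.

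Section 2.5.2 assigns the instrument: "For self-management the Self-management Assessment Scale (SMASc) will be used—patients only". The only timing given is after the intervention. In the control arm, "patients will be asked to complete outcome measures around a month after being sent the digital booklet", which is meant to match the month that the group programme lasts. Section 2.4.2 likewise speaks of post-intervention measures.

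Section 2.6 fixes the comparison of the arms: "To assess differences between two groups, the analyses will be conducted using independent data", by independent t-test or Mann-Whitney U according to distribution, with effect sizes and 95% confidence intervals. It adds that outcomes will be controlled for variables such as age, sex, education and length of intensive care stay. The one regression model it names is logistic, for associations of disease severity and sociodemographic variables with outcomes.

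The only reference to a baseline measurement is in the eligibility text of section 2.3, where patients must be able to "complete baseline/outcome measure". No instrument is named there.

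**The concern.** SMASc is a score that can be taken before the intervention, unlike satisfaction with care. A patient's earlier score on the same scale is a natural covariate for the later one. A two-sample comparison of follow-up scores leaves that information unused, so between-patient variation that existed before randomisation stays in the error term.

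The result has a declared use. Section 2.6 says the sample is adequate to estimate key parameters for designing an RCT. Section 3 says trends in self-management and health outcomes will guide the choice of primary outcomes and the power calculations. For a larger trial with a baseline-adjusted analysis, two of those parameters are the residual SD of SMASc and its baseline-to-follow-up correlation. No stated analysis produces either one.

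**Working it through.** **Inputs from the protocol article.** Section 2.6 gives at least 50 recruited, 25 per arm. This agrees with its screening target: 145 × 0.35 = 50.75. Section 2.6 also gives 20% drop-out as the green limit, which leaves 25 × 0.8 = 20 per arm. The article states no SD, correlation or target precision for SMASc, so there is no planned figure to reproduce for this outcome. Results below are in SD units.

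**Assumption.** The correlation r between baseline and follow-up SMASc is not given. I show 0.3, 0.5 and 0.7. Patients are treated as independent, as the plan treats them.

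**Half-width of the 95% interval.**
- Follow-up only: t(0.975, 2n − 2) × √(2/n).
- Baseline-adjusted: the same × √(1 − r²). The one further degree of freedom lost is negligible.
- Multipliers √(1 − r²): 0.954 (r = 0.3), 0.866 (r = 0.5), 0.714 (r = 0.7).

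At 25 per arm: 2.011 × √(2/25) = 2.011 × 0.283 = 0.57. At 20 per arm: 2.024 × √(2/20) = 2.024 × 0.316 = 0.64.

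| Per arm | Follow-up only | r = 0.3 | r = 0.5 | r = 0.7 |
|---|---|---|---|---|
| 25 | 0.57 | 0.54 | 0.49 | 0.41 |
| 20 | 0.64 | 0.61 | 0.55 | 0.46 |

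The variance falls by r², that is by 9%, 25% and 49%.

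**Size of chance imbalance.** The standard error of the baseline difference at 25 per arm is √(2/25) = 0.28 SD. An imbalance of that size moves the unadjusted follow-up difference by r × 0.283 = 0.08, 0.14 or 0.20 SD. The probability of a baseline difference above 0.3 SD in either direction is 2 × [1 − Φ(0.3/0.283)] = 29%.

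**What the planning parameter is worth.** Take an illustrative larger trial with an assumed effect of 0.3 SD, two-sided 5% level and 90% power. Without baseline, n per arm = 2 × (1.960 + 1.282)² / 0.3² = 234 after rounding up. Multiplying by (1 − r²) gives 213, 176 and 120.

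**How well the pilot could estimate r.** By Fisher's transformation, the interval is tanh[atanh(r) ± 1.96/√(n − 3)]. For an observed r of 0.5 this is 0.26 to 0.68 with 50 patients and 0.22 to 0.70 with 40. The estimate would be rough.

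**The case against.** A reader might infer that no baseline SMASc is collected and that the pilot therefore cannot supply the correlation. The article does not establish this. Section 2.3 implies some baseline measurement, section 2.5.2 does not exclude SMASc from it, and an article may leave the schedule of assessments to the full protocol.

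A reader might also infer that the covariate list shuts baseline SMASc out. It is introduced by 'such as' and is open. Still, none of the named covariates stands in for the score itself, and the one named model is logistic.

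A third tempting reading is that a chance baseline difference would bias the result or pass for a V-CARE effect. Allocation is randomised, so the unadjusted estimator is unbiased, and chance imbalance is part of the sampling error that the planned 95% interval already covers. The loss is one of precision.

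The strongest objection concerns weight. The aim is to explore, section 2.6 disclaims conclusions on effectiveness, and no progression criterion uses SMASc. A larger trial could be sized conservatively without the correlation. The correlation may also be low: recruitment follows the 30-day visit, while groups start around 2 to 3 months and at latest 6 months after discharge, so consent and follow-up may lie months apart in early recovery. At r = 0.3 the gain is small.

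All of this limits the point. It does not remove the fact that a more precise analysis is available at almost no cost, for a result the article intends to use in planning.

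**Conclusion.** The point holds as a modest improvement in precision and planning information. The stated SMASc comparison is valid but uses no pre-intervention score. Baseline adjustment would narrow the 95% interval at 25 per arm from a half-width of 0.57 SD to between 0.54 and 0.41 SD, and at 20 per arm from 0.64 SD to between 0.61 and 0.46 SD. These ranges rest on assumed correlations of 0.3 to 0.7; the lower end offers little and the upper end a good deal. The article leaves open whether baseline SMASc is already collected. If it is, only the analysis needs to change. If it is not, the decision must be made at enrolment, because an analysis plan written later cannot recover the score.

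**What to change.** 1. State in section 2.5.2 whether SMASc is among the baseline measures that section 2.3 mentions. If it is not, add it after consent and before randomisation.
2. In section 2.6, replace the unadjusted SMASc test with a linear model (ANCOVA) of follow-up SMASc on arm and baseline SMASc. Report the adjusted difference with its 95% confidence interval. Keep the exploratory status and the disclaimer on effectiveness.
3. Report the SD, the residual SD and the baseline-to-follow-up correlation with its confidence interval as planning figures, and note that the correlation will be imprecise at this sample size.

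Cost: nothing beyond a text change if baseline SMASc is already collected. Otherwise it is one more self-report questionnaire per patient and a small addition to the protocol. The screening target of 145, the recruitment target of 50 and the three progression criteria stay as they are.
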